**1. Version control**

The table below outlines the changes made to different versions of the protocol.

| Version number | Overview of changes since previous version | Effective date |
|----------------|--------------------------------------------|----------------|
| 1.0            | Nil. Inaugural protocol.                   | 28/11/22       |
| 2.0            | Updated based on feedback from HREC        | 24/1/23        |

159  
160  
  
161  
  
162  
163  
164  
  
165  
  
166  
  
167  
168  
169  
170  
171  
172  
173  
  
174  
175  
176  
177  
178  
  
179  
180  
181  
182  
  
183  
  
184  
  
185  
  
186  
  
187  
  
188

**2. Administrative information**

**2.1 Title**

Identifying the effect of air purifiers in reducing the incidence of Acute Respiratory Infections (ARIs) among residents in Australian Residential Aged Care Facilities (RACFs): A Randomised Control Trial.

**2.2 Trial registration**

The trial will be registered with the Australia New Zealand Clinical Trial Registry (ANZCTR).

**2.3 Funding, sponsors, and partners**

This research is supported by an Australian Government Research Training Program (RTP) Scholarship.

The project is a clinical trial using air purifiers for identifying their effectiveness in reducing the incidence of ARIs in RACFs. Industry partner GAMA Health Care will sponsor air purifiers to support the study. They have no role in the study design, implementation, analyses, interpretation, or publications.

The project also requires statistical support. The guidance on design and statistical analysis will be arranged through Hunter Medical Research Institute (HMRI) Clinical Research Design & Statistics (CReDITSS) unit. The cost involving statistical support will be arranged by the principal investigator as part of the University of Newcastle’s allocation of funding under the Research Training Package.

The project will be conducted in regional Residential Aged Care Facilities (RACFs) in NSW. The facility participation involves approval by a senior executive manager or delegate and/or the governing board. However, no cost is involved in the facility or participant enrolment process for the study.

189 **3. Study team and governance**

190 **Study Team**

191

| Name                                        | Role                                                    | Affiliations                                                           | Expertise                                                                                                            | Responsibility and contributions                                                                          |
|---------------------------------------------|---------------------------------------------------------|------------------------------------------------------------------------|----------------------------------------------------------------------------------------------------------------------|-----------------------------------------------------------------------------------------------------------|
| Associate [name]                   | Co-ordinating Principal Investigator/ Researcher        | University of Newcastle                                                | Student supervision
Quantitative research
Mixed methods
Patient safety
Nursing practice                  | Protocol review and updates
Governance
Student supervision                                          |

209 in older adults above 65 years of age by 2066 (Australian Institute of Health and Welfare  
210 (AIHW), 2021). Age related frailty and related immune senescence are known to be the leading  
211 factors responsible for older adults’ susceptibility to various infections (Jaul & Barron, 2017;  
212 McElhaney et al., 2012; Wang & Casolaro, 2014). Childs et al. (2019) identified that the  
213 residents of RACFs are a highly vulnerable group of older adults and are more prone to get  
214 ARIs than any other population of older people. This is significant because ARIs are a major  
215 health concern among residents of RACFs (Childs et al., 2019).

216 While available data regarding potential routes of transmission is yet to provide clarity on the  
217 extent of transmission through various routes, live viruses and viral RNAs of common  
218 respiratory pathogens such as influenza and respiratory syncytial virus (RSV) have been  
219 identified in the samples of air collected from health care settings (Shiu et al., 2019). Although  
220 older adults in RACFs are susceptible to a variety of viral agents (Shi et al., 2020), influenza and  
221 RSV are known to be clinically important in this frail cohort (Branche & Falsey, 2015; Elliot &  
222 Fleming, 2008; Thompson et al., 2003; van Asten et al., 2012).

223 The transmission routes of various respiratory viruses have been identified as contact, droplet,  
224 and aerosols (Brankston et al., 2007; Leung et al., 2020; Tellier, 2006). However, the spread of  
225 viral agents through aerosols has received more attention over time as it has been noted as a  
226 substantial mode of transmission (Brankston et al., 2007; Leung et al., 2020; Tellier, 2006).  
227 Leung et al. (2020) identified that 35% of influenza viruses isolated were from the samples of  
228 aerosols and was comparably higher than that of the droplet samples. The airborne  
229 transmission can even occur over several metres of distance from the infected subject (Tellier et  
230 al., 2019).

231 Data from a recent study highlights the direct impact of poor indoor air quality in the

development of Severe Acute Respiratory Infections (SARI) and the role of advanced engineering measures in improving the quality of indoor air (Agarwal et al., 2021). This study also addresses the need for a combination of non-pharmacological and engineering measures including the utilization of air purifiers and modified ventilation systems for maintaining a robust indoor environment (Agarwal et al., 2021).

Further extended studies with distinctive research questions that investigate the benefits of the application of engineering measures for maintaining indoor air quality in RACFs have been warranted by Reddy et al. (2021). Also, trial-based projects to identify the pros and cons of employing filtration systems in RACF have been recommended (Reddy et al., 2021).

## 5. Methods

### 5.1 Aim

The study aims to evaluate the effectiveness of air purifiers in reducing the risk of acute respiratory infections (ARIs) among residents in Australian Residential Aged Care Facilities (RACFs).

### 5.2 Design

The proposed study will deploy a multi-centre double-blind randomised two-period two-treatment crossover design to determine the effectiveness of placing air purifiers in the rooms of the residents of RACFs. The overview of the crossover trial of the proposed project has been illustrated in figure.1.

[figure not shown]

(Figure: 1. – study design).

256 5.3 Population and recruitment

257 Study setting

258 The proposed study will be a multi-centre trial. Two residential aged care facilities in a regional  
259 area of New South Wales will be invited to participate in the study. A purposive sampling  
260 approach based on the researcher’s networks will be used to invite facilities.

261 To be eligible for participation, the residential aged care facilities must be accredited by the  
262 Aged Care Quality and Safety Commission (Australian Government Aged Care Quality and  
263 Safety Commission (ACQSC), 2022), be geographically based in New South Wales, Australia,  
264 and have a minimum of 50 residents.

265 Facility enrolment

266 To enrol in the study, the RACF will agree to these requirements:

- 267 1. in-kind support which would include facilitating access to the facility to enable recruitment  
268 including access to electronic and paper forms of potential participants’ medical and  
269 health records, placement of air purifiers, and data collection.
- 270 2. nomination of one staff member as a local point of contact for staff, should any queries  
271 arise.
- 272 3. access to staff and/or communication to staff about the study and their support in keeping  
273 air purifiers turned on.
- 274 4. unless otherwise agreed to in writing, no use, disclosure, copying, or distribution of study  
275 materials or outcomes.

276 Participant recruitment

277 For potential participants who have the ability to provide informed consent, this will be sought.  
278 Mini-Mental State Examination (MMSE) (Folstein et al., 1975; Folstein et al., 1983) will be used  
279 to assess participants’ ability to provide informed consent where required. For potential  
280 participants who lack the capacity to provide informed consent, a member of the research team  
281 will discuss the study with their representative, enduring power of attorney, or legal guardian  
282 (Information and Privacy Commission ( IPC), 2021). In such circumstances, informed consent  
283 will be obtained from the relevant person with the authority to provide consent on behalf of the  
284 resident (Commonwealth Department of Health and Aged Care, 2015). The potential  
285 participants’ guardians will be encouraged to discuss the research with the potential participant  
286 if the participants are able to understand what the study involves, based on their level of

287 cognitive impairment. Then it should be a joint discussion on whether the individual should  
288 participate in the study or not.

289 Participation in this study is entirely voluntary. This means that the participants do not need to  
290 agree to take part in the research, and participants' or their guardians' refusal to take part will  
291 also be respected. If any party decides to take part, they can still withdraw from the study at any  
292 time without having to give reasons for their choices/decisions. In such circumstances, any data  
293 collected concerning participants, or their guardians will be withdrawn from the study. Whatever  
294 the decision may be, the participants will be assured that it will not affect their treatment or  
295 relationship with the staff of the facility who are caring for the participants. Of the people caring  
296 for the participants, only the nursing staff and the members of the research team will be aware  
297 of participation or non-participation.

298 Potential participants who meet the eligibility criteria will be provided with information about the  
299 study. A member of the research team will follow up with potential participants to determine their  
300 interest in participating in the study. The follow-up period will be at least 3 days post-initial  
301 contact to allow participants time to consider participation.

302 Sometimes during the course of a study, new information becomes available about the  
303 treatment that is being studied and the participants will be kept informed of any significant new  
304 findings which may affect their willingness to continue in the study.

305 In circumstances where the potential participants require public guardians' approval since they  
306 are unable to provide consent, they will be excluded from the study.

307 In the enrolled facilities, a member of the research team will provide information to residents or  
308 their guardians about the study in paper forms. This will include the study requirement for  
309 accessing participants' electronic and paper forms of medical and health records managed by  
310 the enrolled facilities for obtaining information relevant to the study. This member of the  
311 research team will be available to answer any questions.

312 [Participants' eligibility Criteria](#)  
313 [Inclusion criteria](#)

314 Participants must meet the following criteria to be included in the study. At the time of project  
315 commencement; the participants must:

- 316     ○ be a permanent resident of an Australian Residential Aged Care Facility enrolled in the  
317         study
- 318     ○ reside in their private room (i.e., not a shared room)

- not be on palliative Trajectory-C comfort care

#### Exclusion criteria

Potential participants may be excluded from the study if at the time of project commencement, they:

- are respite residents
- reside in shared rooms
- are on palliative Trajectory-C comfort care
- are unable to provide consent and require public guardian approval

#### 5.4 Enrolment

Once ethics approval and governance approvals are in place, the facility will be officially enrolled. It is anticipated that governance approval will include approval by a senior executive manager or delegate and/or the governing board.

A participant will be considered enrolled in the study if they meet the eligibility criteria and once informed written consent has been obtained as necessary. Random allocation to the control or intervention arm of the study will only occur for enrolled participants.

#### Individual participants

The procedure of installing the air purifiers in participants' rooms will be mutually agreed upon between the research team and the potential participant or their nominated responsible person (enduring power of attorney or legal guardian). The final decision to participate in the study will be based on the best interest of the individual resident. Informed consent will be sought from each potential participant or their nominated responsible person (enduring power of attorney or legal guardian) before participating in the study. However, the potential participant or their nominated responsible person (enduring power of attorney or legal guardian) will have the option to withdraw from the study at any stage of the project. The participants will be randomly allocated into the intervention or control groups.

#### Delays

If there is a serious national epidemic during the trial, the study will continue to collect data, but any planned changeovers to the intervention will be delayed until it is possible to recommence. This is a practical move as the facility management and the staff will likely be diverted away from the research intervention in the case of a serious outbreak. An epidemic also has the potential to be a confounder of our primary and secondary outcomes, and so delaying the change from control to intervention will reduce the correlation between the epidemic and the intervention. If a participating facility fundamentally changes its case mix or similar impact as a result of an epidemic (e.g., influenza, RSV, or other ARI virus), the research team would decide

on how to handle this scenario based on the detail at the time. Options would include excluding data collected from that facility from analysis and/or stopping data collection from the facility. Any decision from the research team would need to consider risk (personal, residents, community), public health and government requirements or directives, and impact on the quality of the study.

Discontinuation of study or study site

The study will be discontinued if a regulatory body, funding body, or Human Research Ethics Committee (HREC) judges it necessary for medical, safety, regulatory, or other reasons consistent with applicable laws, regulations, and good clinical practice.

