5.12 Confounders

The proposed project will identify the effect of air purifiers in reducing the ARIs in RACFs through aerosol filtration. The study will only measure the activities and aerosol exposure in the rooms of residents in enrolled facilities. The potential confounder may be the resident's exposure to aerosols outside the rooms such as communal and shared areas including recreation rooms, lounges, dining areas, and double rooms since these will not contain air purifiers. Each resident's mobility status will be captured as part of baseline demographic data and in routine data collection each 2 weeks to document changes in mobility patterns over the course of the study. In addition, a cross-sectional audit of each resident's movement on a 'typical' day will be captured during each phase of the study. This data will be quantified to estimate the average amount of time a resident spends outside their room each day in hours. Any treatment for an ARI using antiviral or antibiotic may also be considered as another confounder. Hence, any participants who are on treatment for an ARI throughout the trial period will also have this treatment monitored and documented accordingly. Routine data collection will include changes to current medications (including cytotoxic, antibiotics, and antivirals) to ensure this potential confounder is captured and quantified.

An epidemic also has the potential to be a confounder of primary and secondary outcomes.

6. Monitoring

The member of the research team blinded to the intervention will be responsible for fortnightly data collection. The data collection and the trial processes will be monitored by the members of

670 the research team who are the supervisors of the project. Data will be reviewed to ensure the  
671 correct collection of the data sets and implementation of the intervention. Support (site visits,  
672 telephone, and email contact) will be provided by the study staff as required during the  
673 intervention phase to check core trial processes and maintain data quality.

674 **6.1 Safety evaluations**

675 It has been assumed that the project will only involve negligible risk to any human participants  
676 which means there will be no foreseeable risk of harm or discomfort; and any foreseeable risk  
677 will be no more than an inconvenience (National Health and Medical Research Council  
678 (NHMRC) et al., 2018b). The study will not involve any invasive procedures, but each  

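### The epidemic delay rule names only the change from control to intervention; followed literally in this two-sequence crossover, it would put both sequences on control during an epidemic and favour the purifier.

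*Protocol*

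**What the plan says.** Protocol section 5.2 describes a "double-blind randomised two-period two-treatment crossover design". Section 5.8 allocates residents 1:1 to the two sequences, in blocks stratified by site. Section 5.5 sets two phases of three months with a one-week washout between them. In that week, residents finishing control gain a HEPA filter and residents finishing the intervention lose theirs.

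The Delays text in section 5.4 covers an epidemic:

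- Data collection goes on: "If there is a serious national epidemic during the trial, the study will continue to collect data".
- The changeover rule is that "any planned changeovers to the intervention will be delayed until it is possible to recommence".
- The practical reason concerns staffing: "This is a practical move as the facility management and the staff will likely be diverted away from the research intervention".
- The statistical reason is that "delaying the change from control to intervention will reduce the correlation between the epidemic and the intervention".

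Both the rule and its statistical reason name the move onto filtration. Neither there nor in section 5.5 does the protocol say what happens in an epidemic to residents due to move off filtration.

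Section 5.10 times the changeover for the peak of the influenza season. The primary model in section 5.11 is a mixed logistic regression with treatment, collection time, crossover characteristics and site, and a random intercept per resident.

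**The concern.** The rationale suits a one-way rollout, in which everyone starts on control and later moves to the intervention. There, calendar time and treatment are entangled, and holding back the switch might be argued for. In this trial the two sequences run side by side within each site. At any date about half of the residents have filtration and half do not, so randomisation already separates an epidemic from treatment as long as both sequences are handled alike.

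A delay in one direction breaks that balance. Control-first residents remain on control and intervention-first residents join them. The excess infections then belong to control in phase 1 for one sequence and to control in phase 2 for the other. They follow treatment and not phase, so a phase term cannot absorb them, and neither can a site term. The bias runs towards showing that the purifier works, and the rule would have produced the very correlation that it is meant to reduce.

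**Working it through.** **The plan's own figure.** Inputs from section 5.7: discordant proportions 0.12 and 0.32, two-sided 5% level, 80% power.

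- Odds ratio = √[(0.12 × 0.12)/(0.32 × 0.32)] = 0.375.
- n per sequence = (1.960 + 0.842)² × 0.25 × (2/0.12 + 2/0.32) / (ln 0.375)² = 46.74, so 47 per sequence and 94 in total.

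The stated sample size is reproduced, and 0.375 is the yardstick for the spurious effects below.

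**Inputs for the check.** From the protocol: 40% infected per control phase, and three months taken as 13 weeks. Assumed, because the protocol gives none: an epidemic that starts at the planned changeover, lasts D weeks (also the length of the delay) and multiplies the weekly hazard by k. Also assumed: constant hazard otherwise, no true treatment effect, a full 13-week second phase at ordinary hazard for control-first residents, and the washout week ignored.

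Weekly hazard h = −ln(0.6)/13 = 0.0393. Risk over w week-equivalents = 1 − exp(−h·w). Both treated phases have risk 0.40 (odds 0.667).

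**One-way delay, lengthened phase 1 counted in full.** Control-first residents accumulate 13 + kD week-equivalents in phase 1. Intervention-first residents accumulate (13 − D) + kD in phase 2, on control.

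| D, k | Control risk, phase 1 | Control risk, phase 2 | OR, phase 1 | OR, phase 2 | Geometric mean |
|---|---|---|---|---|---|
| 2 weeks, 1.5 | 16 weeks: 0.467 | 14 weeks: 0.423 | 0.76 | 0.91 | 0.83 |
| 4 weeks, 2 | 21 weeks: 0.562 | 17 weeks: 0.487 | 0.52 | 0.70 | 0.60 |

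For the second row: 0.667/(0.562/0.438) = 0.52; 0.667/(0.487/0.513) = 0.70; √(0.52 × 0.70) = 0.60.

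**One-way delay, only the planned 13 weeks of phase 1 counted.** The phase 1 odds ratio becomes 1.00 and phase 2 is unchanged.

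- 2 weeks, 1.5 times: √(1.00 × 0.91) = 0.95.
- 4 weeks, 2 times: √(1.00 × 0.70) = 0.84.

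**Longer control phase alone.** With a 4-week delay, no rise in hazard and full counting, phase 1 control risk is 1 − exp(−17h) = 0.487. The odds ratios are 0.70 and 1.00, geometric mean 0.84.

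**Both sequences treated alike (4 weeks, 2 times).**

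- Both delayed: phase 1 risk is 0.562 in each sequence and phase 2 risk is 0.40 in each, so the odds ratio is 1.00.
- Neither delayed: 0.40 in each sequence in phase 1 and 0.487 in each in phase 2, so again 1.00.

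**False-positive rates**, from simulated trials with 47 per sequence and no true effect:

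- 2-week case, counted in full: about 9%.
- 4-week, 2-times case, counted in full: 37% with the crossover odds-ratio estimator, 43% with a model containing treatment, phase and site.
- 4 weeks, no rise in hazard, counted in full: about 8%. Its odds ratio is 0.84, the same as the 4-week, 2-times case on the 13-week count.
- Both sequences treated alike: at or below the nominal 5%.

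**The case against.** The strongest reply is that the protocol never says that only one direction is delayed. A reader might infer that it requires filters to be removed on schedule during an epidemic; the text does not support that. It is silent on the reverse change, and several features point to one joint changeover. Diverted staff would hold up both kinds of change. Section 5.5 places both in one washout week and speaks of swapping devices between groups. Changing only half of the residents could also reveal allocation, which sections 5.5 and 5.9 set out to prevent. This stands as a limit on how likely the harm is. It does not clear the text, because the rule and its statistical reason both name one direction, and site staff could follow them as written.

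The trigger is also narrow: a serious national epidemic that spans the single changeover. The influenza peak in section 5.10 is the season the trial was timed around and is not itself that trigger. That is fair. The size depends as well on how a lengthened phase is counted, which an SAP not at hand may settle; hence both counts are shown.

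Two stronger readings should not be drawn. First, because "Options would include excluding data collected from that facility from analysis", a reader might infer that a site can be dropped for having had infections, which would bias the result. The stated trigger is a fundamental change in case mix or similar impact, and exclusion is one option among several. Randomisation is stratified by site, and allocation stays blinded until just before the final analysis. Removing a whole site therefore removes both sequences together: it costs information, but no bias in the treatment effect has been shown. Second, the statement in section 5.12 that "An epidemic also has the potential to be a confounder of primary and secondary outcomes" speaks of potential only and need not be deleted.

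**Conclusion.** The point holds as a conflict between the Delays rule and the two-sequence design. Followed literally during an epidemic that spans the changeover, the rule biases the primary odds ratio towards the purifier, and the planned phase and site terms cannot correct it. In the assumed scenarios the spurious odds ratio is 0.83 to 0.60 with the lengthened phase counted in full and 0.95 to 0.84 with 13 weeks counted, against a design effect of 0.375. These figures rest on an assumed duration, hazard multiplier and start date, and on the reverse change going ahead as scheduled. The documents do not establish that it would; they fail to rule it out, and the reason they give points that way.

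**What to change.** Reconcile the Delays text in section 5.4 with the changeover described in section 5.5. State that any epidemic delay applies to both sequences at a site on the same date, and that phases run to the actual changeover date in both. Remove the claim that delaying the control-to-intervention change reduces the correlation between epidemic and intervention; the staffing reason can stand alone. No further model term is needed.

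The cost is a short protocol amendment. If a delay occurs, phase 1 is longer in both sequences, which the phase term already in the model accommodates.

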## 5.6 Outcomes

### Primary outcome

The primary outcome is a reduction in the occurrence of ARIs. Each participant will have a binary outcome, no infection, and infection, for their control and intervention study period. The case definition for Acute Respiratory Infection (ARI) is the sudden/acute onset of at least one of the following four respiratory symptoms:

- cough
- sore throat
- shortness of breath
- coryza

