### AND

- a clinician's judgement that the illness is due to an infection (European Centre for Disease Prevention and Control (ECDC), 2018). This definition is consistent with World Health Organization (WHO) Regional Office for Europe (2011).

An ARI will then be categorised as one of the following:

- ARI, no diagnostic test performed: Residents presenting with symptoms as identified by the definition of ARI and eligible to be categorized as an ARI case.
- ARI, influenza (A and B): Residents presenting with symptoms of ARI and confirmed influenza (A and B) by diagnostic lab tests.
- ARI, SARS Cov2: Residents presenting with symptoms of ARI and confirmed SARS Cov2 by institutional RAT or diagnostic lab tests.
- ARI, rhinovirus: Residents presenting with symptoms of ARI and confirmed rhinovirus by diagnostic lab tests.

- ARI, respiratory syncytial virus: Residents presented with symptoms of ARI and confirmed RSV by diagnostic lab tests.
- ARI, adenovirus: Residents presenting with symptoms of ARI and confirmed adenovirus by diagnostic lab tests.
- ARI, diagnostic test performed but no virus identified

Participants in the study will not be subject to a diagnostic test as part of the study. Any diagnostic tests will be determined as part of their medical care, facility procedure, or usual practice. We expect any ascertainment bias to remain constant throughout the study i.e., the same in both phases.

Secondary outcomes

The secondary outcomes of this study are:

- Time to first infection for participants. This will be defined as time in days since the commencement of the study phase to the diagnosis of ARI.
- The number of visits to an emergency department due to an ARI
- The number of hospital admission due to an ARI. A hospital admission is defined as being admitted to a hospital and having at least one overnight stay.
- The number of medical consultations including GP and NP reviews due to an ARI. A consultation will be defined as a billable visit to a medical or nurse practitioner and/or where a medical or nurse practitioner has documented an assessment related to an ARI in the participants' medical notes at the facility.

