## 5.8 Randomisation and concealment

Prior to the enrolment of participants, all air purifiers in the study will be pre-labelled. Air purifiers will either have a HEPA filter removed (control) or will have the air purifier remain in place (intervention). A database listing the air purifier (label) and whether it is a control or intervention will be established. This database will be held by one researcher (researcher 1) not involved in the enrolment (including recruitment and consent), data collection, or decisions regarding the outcome. Other members of the research team will enrol participants. When a participant is enrolled, the researcher will notify researcher 1 of their name. No other baseline or demographic data will be provided.

Researcher 1 will randomise participants using a protocol of block randomisation stratified by site. This approach will ensure an even balance of participants in the intervention and control arms at each site. Randomisation will occur in a 1:1 ratio into one of the two sequences of intervention and control groups using a computer-generated randomisation schedule. Allocation concealment will be ensured as the same researcher will not disclose the outcome of randomisation to the remainder of the team and will hold the allocation in a password-protected database on a file not accessible to the remainder of the team. Upon the immediate commencement of the trial at a site and after all baseline data is collected, researcher 1 will inform the remainder of the team of which air purifier should be provided to which participant. As air purifiers are already pre-labelled, researchers allocating the air purifiers to participants will not be able to visually tell whether an air purifier has a filter (intervention) or not (control).

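### Section 5.4 lets the research team exclude a facility's already collected data after an epidemic of the infections the trial counts, with no rule set in advance and only two facilities planned

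*Protocol*

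**What the plan says.** The clause stands in Section 5.4 of the protocol, under Delays. Its trigger reads "If a participating facility fundamentally changes its case mix or similar impact as a result of an epidemic", with influenza, RSV or another ARI virus given as examples. The research team would then decide "on how to handle this scenario based on the detail at the time". On the choices open to it, the text says: "Options would include excluding data collected from that facility from analysis and/or stopping data collection from the facility". The team must weigh risk, public health and government requirements, and study quality. No threshold is given, and the text does not say which members decide.

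Four other places bear on this:

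- Section 5.6: "The primary outcome is a reduction in the occurrence of ARIs". Influenza, SARS-CoV-2 and RSV are named categories of that outcome, for example "ARI, influenza (A and B): Residents presenting with symptoms of ARI and confirmed influenza (A and B) by diagnostic lab tests".
- Section 5.3 (Study setting): "Two residential aged care facilities in a regional" area will be invited. Each must be accredited "and have a minimum of 50 residents". Participant numbers per site are not stated.
- Section 5.8: "Researcher 1 will randomise participants using a protocol of block randomisation stratified by site", in a 1:1 ratio to the two sequences.
- Section 5.10: a researcher screens every participant's records for ARI each fortnight.

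**The concern.** Which data enter the primary analysis should not be open to choice once outcome data are accumulating. Here the event that opens the choice is an epidemic of the same infections the trial counts. The people choosing may know how many infections each facility has had, and the criterion for choosing is left open. Even if the choice is made in good faith, a reader of the results could not tell whether the analysis set was fixed independently of the data.

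The clause also does little to protect the treatment comparison. An epidemic at a site reaches residents of both sequences at the same time, so it does not by itself favour one treatment. With only two sites, one such decision would turn a two-site trial into a single-site one and remove a large share of its information.

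**Working it through.** **Does the epidemic require exclusion?** Randomisation is 1:1 to sequence within site (Section 5.8), and both sequences run concurrently. During a local outbreak, some residents at that site have the filter and others do not. The planned model (Section 5.11) has a fixed effect for site, a term for study collection time and a random intercept per participant. Participants lost are to be handled by multiple imputation, or by censoring in the time-to-infection analysis. So the within-site comparison is protected from the epidemic as a common exposure, provided that any delayed changeover applies to both sequences at that site. Section 5.4's own main rule for a serious national epidemic is that data collection goes on.

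**Who decides?** Section 5.9 blinds the participant and the researcher who determines the outcome. Researcher 1 holds the allocation list (Section 5.8), and another role changes the filters (Section 5.5). Section 5.4 says only that the research team decides.

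**What is lost? Inputs (Section 5.7 and its Figure 2):** two-sided alpha 0.05, power 0.80, control proportion 0.40, treatment proportion 0.20, discordant proportions 0.12 and 0.32 in one sequence and 0.32 and 0.12 in the other.

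*Reproducing the stated sample size.*

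- OR = (0.2/0.8)/(0.4/0.6) = 0.375, and |ln OR| = 0.981.
- s² = ¼ × (1/0.12 + 1/0.32 + 1/0.32 + 1/0.12) = 5.729.
- n per sequence = (1.960 + 0.842)² × 5.729 / 0.981² = 46.74, rounded up to 47. The total is 94, as stated.

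*Power with fewer participants.* Power = Φ(|ln OR| / √(s²/n) − 1.96), where n is half the number remaining.

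| Participants remaining | Excluded | \|ln OR\|/SE | Power |
|---|---|---|---|
| 94 | 0 | 2.81 | 80.2% |
| 60 | 34 (36%) | 2.24 | 61.2% |
| 47 | 47 (50%) | 1.99 | 51.1% |
| 34 | 60 (64%) | 1.69 | 39.3% |

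The splits are assumptions, because the protocol gives no per-site numbers. A simulation from the same discordant proportions, with 0.5 added to each discordant count, gave 83% at 94 participants, 48% at 48 and 45% at 46. The fall is of the same order.

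**The case against.** The clause is a contingency. It needs an epidemic, then a fundamental change at the facility or something like it, and then a decision to exclude rather than take another course. Dropping a whole site removes both sequences together, so the remaining site's comparison is still randomised. An epidemic may also divert staff from the intervention, as Section 5.4 itself expects, and concurrent sequences do not guarantee that the purifiers were kept running. Analysis sets are often left to a statistical analysis plan.

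Most of this stands as a limit on the point, but it does not remove it. Poor delivery during a disrupted period is a reason for a sensitivity analysis, not for an open choice about the primary one. An analysis plan may add rules, but the protocol itself authorises the exclusion.

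Some stronger readings are tempting but not supported:

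- *A high infection count triggers exclusion.* The stated trigger is a change in the facility caused by an epidemic. It is related to the outcome but is not a count of it.
- *The decision would be made unblinded.* Section 5.8 keeps researcher 1 out of data collection and outcome decisions and bars disclosure of allocation to the rest of the team. The gap is only that the clause does not say who decides.
- *Most of the events would be lost.* No figure in the protocol supports this.
- *Safety checks would end if data collection stopped.* Section 6.1 also runs them through contact with nominated facility staff, and Section 5.5 has staff check the units at least monthly.

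**Conclusion.** The point holds. The protocol allows collected outcome data from a whole facility to be removed from the analysis, on an undefined trigger linked to the outcome, by a group not limited to blinded members. The epidemic as such does not require this. A directional bias is possible but is not shown.

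The quantifiable harm is lost power: from 80% to about 51% if one of two equal facilities is dropped, and 61% to 39% for the unequal splits shown. These figures assume that the protocol's discordant proportions hold at the remaining site, that the excluded site would otherwise have given complete data, and that there is no dropout. The stated inputs reproduce 94 without any allowance for dropout, although Section 5.11 expects loss to follow-up to be likely, so power in practice could be lower both before and after an exclusion.

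**What to change.** In Section 5.4, under Delays:

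1. Delete the option to exclude data already collected.
2. State that all data collected up to any pause or stop at a facility stay in the primary analysis.
3. State that an analysis without the affected facility or period is a sensitivity analysis only.
4. State that any such analysis decision is made by members blinded to allocation and is documented before unblinding.

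This concerns the analysis only. It leaves open when a facility should pause or stop.

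The cost is a few sentences in an amendment. The downside is small: data from a disrupted period, possibly with poorer delivery of the intervention, stay in the primary analysis and may dilute the effect or add noise. The sensitivity analysis would show how much.
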